#### Secondary End Point Analysis

We will evaluate the change in behavioral health status and PrEP knowledge before and after the intervention and construct 95% CIs. Generalized linear mixed effect models will be used to reassess the intervention effect on these measurements while adjusting for the baseline characteristics age, gender, and other demographics. Finally, the same analysis will be applied to the 3-month postintervention follow-up measures to determine the long-term effects of the intervention. These estimated parameters allow reliable estimates of sample size, power, and detectable effects for the subsequent study.

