### Phases 7 to 8: Training and RCT Pilot Study

#### Procedures

We plan to conduct a 2-arm, randomized controlled study via mobile phones among adolescents in the greater Masaka region of Uganda. We will compare Kirabo to an inactive control and evaluate whether adolescents who interacted with Kirabo had higher rates of self-reported HIV testing (yes/no; verified with the HIV clinic when possible) immediately after the intervention and at the 3-month follow-up assessment. Secondary outcomes include differences in condom use, PrEP knowledge, PrEP uptake for eligible patients, HIV-related knowledge and sexual risk behaviors, and antiretroviral treatment uptake for eligible patients. Exploratory aims include the number of participants who screen positive for symptoms of depression, anxiety, and hazardous alcohol use and the proportion of confirmed linkages to mental health counseling.

Adolescents (aged 15-19 years) in the greater Masaka region in southern Uganda who own a mobile phone will be eligible for the trial. Adolescents will be involved in the trial for approximately 5 weeks with a 3-month follow-up assessment (Figure 2). After informed assent and parental permission, the baseline assessment, and confirmation of eligibility, adolescents will be randomly assigned to the Kirabo intervention group or standard of care group. Randomization will be performed in a 1:1 ratio and stratified by gender and school (to minimize contamination) with a block size of 10. We anticipate recruiting students from 20 schools. The treatment assignments will be generated using a pseudorandom number generator. An electronic list of IDs, access codes, and credentials will be provided securely to the sites.

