### Statistical Analysis

#### Primary and Secondary Outcomes and Analysis

Summary statistics will be used to describe all metrics and compare them between the students receiving Kirabo and those in usual care at baseline, 1-month postintervention assessment, and the final 3-month follow-up assessment. Means and SDs will be used for continuous outcomes, followed by box plots, and frequency tables will be used for binary and categorical metrics. The primary analysis of this RCT will test whether postintervention HIV testing rates among the adolescents who interacted with Kirabo are significantly higher than those who received standard of care. We will use a generalized linear mixed model to determine statistical significance. In the model, the outcome is the binary indicator of whether an adolescent received an HIV test during or immediately after the intervention. We will also examine the differences between the model at the 3-month follow-up. The main predictor is the intervention assignment (Kirabo or usual care). The school will be included in the model as the random effect to adjust for within-school correlations. We will apply similar analyses to investigate the impact of Kirabo on the secondary outcomes.

Depending on the nature of the outcome, we will use different link functions in the generalized linear mixed model. We will use the identity link for continuous outcomes, the logistic link for binary outcomes, and the log function for ordinal outcomes. For incidence/frequency outcomes, a log function with adjustment for exposure time will be used. We will formally test whether the students in the 2 intervention groups have comparable baseline characteristics, including demographic factors, moderators, and variables measuring potential mechanisms of action (Table 2). If any of these variables are significantly different at baseline, they will be included in the model to adjust for their potential confounding effects.

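### The secondary end point analysis does not say whether its before-after 95% CIs are within or between arms, and its model omits the baseline value of the outcome

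*Protocol article*

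**What the plan says.** Secondary End Point Analysis sets out three steps.

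- First: "We will evaluate the change in behavioral health status and PrEP knowledge before and after the intervention and construct 95% CIs". No arm or comparator is named.
- Second, with a covariate list that ends in unspecified demographic variables: "Generalized linear mixed effect models will be used to reassess the intervention effect on these measurements while adjusting for the baseline characteristics age, gender, and".
- Third: "the same analysis will be applied to the 3-month postintervention follow-up measures to determine the long-term effects of the intervention". The section closes by saying that the estimated parameters will support sample size and power calculations for the subsequent study.

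Other sections bear on how this is read.

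- Procedures gives the design: "We will compare Kirabo to an inactive control", and "Randomization will be performed in a 1:1 ratio and stratified by gender and school (to minimize contamination) with a block size of 10".
- Primary and Secondary Outcomes and Analysis specifies a generalized linear mixed model with school as random effect. It says "The main predictor is the intervention assignment (Kirabo or usual care"), and then "We will apply similar analyses to investigate the impact of Kirabo on the secondary outcomes". It adds a baseline variable to the model only if the arms differ significantly on it.
- Table 2 lists PHQ-9, GAD-7, AUDIT-C and PrEP knowledge at baseline and again immediately after the intervention.
- Primary End Point Analysis for the Pilot RCT, by contrast, includes baseline depression, anxiety and alcohol use among the covariates for HIV testing.

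**The concern.** There are two separate weaknesses.

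**The target of the interval is not stated.** A 95% CI for change over time in one arm tests whether scores moved. A 95% CI for the difference in change between arms tests whether Kirabo moved them more than control did. The sentence fits either reading. The next sentence says the model will look at the intervention effect again, which can suggest that the interval was a first assessment of that effect. Scores can shift in both arms for reasons unrelated to Kirabo: everyone answers the same 13-item PrEP questionnaire twice, and PHQ-9 and GAD-7 refer only to the past 2 weeks. A within-arm interval would pick up such shifts.

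**The model leaves out its most useful covariate.** The baseline value of a score is usually the strongest predictor of its follow-up value. It is collected for each of these measures but is not in the listed covariates. The general rule elsewhere would bring it in only after a significant baseline difference. That is a poor criterion, because the gain in precision depends on correlation with the outcome and not on chance imbalance. In a pilot whose estimates are meant to size a larger trial, unnecessarily wide intervals matter.

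**Working it through.** The documents state no power or precision figure for these secondary end points, so there is none to reproduce. The check has a textual part and an arithmetic part.

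**Textual.** The first sentence of Secondary End Point Analysis gives an interval without a comparator. The general section makes assigned arm the main predictor, extends similar models to the secondary outcomes, and states "Summary statistics will be used to describe all metrics and compare them between the students receiving Kirabo and those in usual care at baseline" and at both later assessments. In a between-arm contrast, a shift common to both arms cancels. So a valid analysis is available, but the secondary section does not tie its 95% CI to it.

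**Precision: inputs.** From Effectiveness Power Analysis: n = 100 per arm. Assumed, because the documents give no values: a continuous score with SD 1 at both times, a true effect of 0.4 SD, correlation r between baseline and follow-up of 0.5 (range 0.3 to 0.7), two-sided alpha 0.05, and no school clustering.

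**Formulas.** With standardized effect e, power ≈ Φ(e × √(n/2) − 1.96), and √(100/2) = 7.071.

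- Follow-up score only: e = 0.4.
- Change score: e = 0.4 / √(2(1 − r)).
- Follow-up score adjusted for baseline (ANCOVA): e = 0.4 / √(1 − r²).

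**At r = 0.5.**

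- Follow-up only: 0.4 × 7.071 = 2.828; Φ(0.868) ≈ 0.81, or 0.80 with the t distribution.
- Change score: √(2 × 0.5) = 1, so e is again 0.4 and power is the same, 0.80.
- ANCOVA: 0.4 / 0.866 = 0.462; 0.462 × 7.071 = 3.266; Φ(1.306) ≈ 0.90.

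A simulation with 20,000 replicates agrees: 0.803 for follow-up only and 0.897 for ANCOVA.

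**Over the assumed range of r (t distribution).**

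| r | Follow-up only | Change score | ANCOVA |
|---|---|---|---|
| 0.3 | 80% | 66% | 84% |
| 0.5 | 80% | 80% | 90% |
| 0.7 | 80% | 95% | 98% |

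ANCOVA is at least as powerful as either alternative in every row. At r = 0.5 its interval is √(1 − 0.25) = 0.87 times as wide as the follow-up-only interval.

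**Risk of misreading.** Suppose Kirabo has no effect and both arms shift equally, with r = 0.5. The Kirabo-arm before-after 95% CI excludes zero in about 16%, 51% and 84% of simulated trials for shared shifts of 0.1, 0.2 and 0.3 SD (assumed). The between-arm comparison stays near 5% throughout. These figures show what a within-arm interval would do if it were read as evidence of effect. They are not the error rate of the plan as written.

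**The case against.** A reader might infer that the plan will treat any change over time shared by both arms as an effect of Kirabo. The documents do not support that. The general section puts assigned arm in the model as main predictor and applies similar models to the secondary outcomes, of which PrEP knowledge is one by name in Procedures. The secondary section itself assigns the intervention effect to a mixed model. Its two steps can also be read as parallel to the primary end point, where an unadjusted arm comparison is followed by an adjusted model; the before-after interval could then be an unadjusted between-arm comparison of change. The statements about long-term effects and about the next trial follow the model sentence and may refer to the model alone. All of this stands, and it removes the claim of a built-in bias.

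On the baseline score, it can be said that follow-up, change-score and baseline-adjusted comparisons are all valid under randomization, that the covariate list is evidently condensed, and that a mixed model could use baseline as a repeated measure. Validity is conceded. It does not make the analyses equally precise, as the table shows. If baseline enters as a repeated measure, most of the loss disappears, but the text does not say so. What it does say is a list of demographics here and a significance-triggered rule elsewhere, while the primary end point model includes several baseline scores outright.

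The stakes are moderate. Acceptability and feasibility are the pilot's declared main purpose, and the behavioral health screening counts are exploratory in Procedures.

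**Conclusion.** The point holds as one of unclear specification and avoidable loss of precision. The section leaves open what its 95% CI estimates, and its stated covariates omit a baseline score that is already collected.

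The size is about 10 percentage points of power (80% to 90%) for a 0.4 SD effect with 100 per arm at r = 0.5. The gain over an analysis of the follow-up score alone runs from about 4 points at r = 0.3 to about 18 at r = 0.7. The effect size, the correlation, normal scores and the absence of school clustering are assumptions. The risk of misreading within-arm intervals is secondary. It arises only if they are reported as evidence on Kirabo, which the wording permits but does not require.

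**What to change.** Reword Secondary End Point Analysis along these lines:

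> For each behavioral health score and for PrEP knowledge we will estimate the between-arm difference (Kirabo minus control) at the postintervention assessment, with a 95% CI, from a mixed model of the follow-up score on assigned arm, the baseline value of the same score, gender and age, with school as random effect. The baseline value is included regardless of any test of baseline differences. Within-arm changes are reported descriptively only.

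Use the same contrast for those measures that are collected at 3 months, and state that only the between-arm estimate will inform planning of the next trial.

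The cost is wording in the analysis section. No added participants, visits or instruments are needed. A between-arm interval will be wider than a within-arm one, but it answers the trial's question.

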#### Mixed Methods Implementation Analysis

We will use mixed methods, including systematic coding informed by CFIR [95,96], surveys, and paradata, to identify the specific elements of Kirabo that we hypothesize will be predictive of successful implementation [98]. This approach will inform the evaluation of the complex processes that motivate adolescents in underresourced settings to seek care. We will transform qualitative data into quantitative data for adolescent responses pertaining to the variables that IMB and CFIR dictate will be predictive of implementation outcomes. For instance, we will focus on constructs in adolescent KII responses that relate to perceived risks and benefits of care for mental health and alcohol use problems. In addition, for specific constructs, we will incorporate technological data, qualitative data, and referral to care data. We will then link users’ actual paradata from their texts (eg, the number of intervention messages viewed) with our adapted m4RH program to their KII responses, survey responses on the perceptions of risk behavior before and after the intervention, and service-seeking rates. This approach will offer a deeper and complex understanding of the ways in which adolescents’ beliefs impact their decision to seek care.

### Ethical Considerations

The research staff obtained written informed consent from adolescents aged ≥18 years and personal assent and permission from adult parents/guardians for adolescents aged <18 years before study enrollment. The consent processes for adults and children were performed separately to avoid coercion. Both consent and assent forms were translated into Luganda (the most widely spoken local language in the study region) and back-translated into English to ensure consistency. Both the assent and consent processes were conducted verbally in Luganda, given that some caregivers and adolescents were illiterate. The study team received training on Good Clinical Practice (GCP) so that sensitive research activities could be handled appropriately. In addition, all interviewers completed the Collaborative Institutional Training Initiative (CITI) certificate and National Institutes of Health (NIH) certificate for the protection of research participants. All study procedures were approved by the NYSPI Institutional Review Board (IRB), the home institution of the principal investigator (PI), and the in-country local ethics board of the Uganda Virus Research Institute (UVRI; reference number GC/127/835). The ethics protocol was also reviewed and approved by the Uganda National Council for Science and Technology (UNCST; reference number SS969ES). This study was registered at ClinicalTrials.gov (NCT05130151).

### Adverse Events and Safety Monitoring

The study will maintain records of adverse events and any referrals for counseling as well as copies of the consent and assent forms. All records will be maintained in a locked filing cabinet at the ICHAD Uganda field office and will be accessible only to the research team. The PI will be responsible for data security and record keeping. The data sets used for analysis will not contain any identifying information, specifically the names and addresses of the participants.

The HIV Center for Clinical and Behavioral Studies has a Performance and Safety Monitoring Board (PSMB) that consists of an independent group of experts. Currently, the members are [name] (chair), [name], [name], and [name]. The members of the PSMB serve in an individual capacity and provide their expertise and recommendations for studies involving human participants. The primary responsibilities of the PSMB are to (1) periodically review and evaluate the accumulated study data for participant safety; study conduct and progress; and, when appropriate, efficacy and (2) make recommendations concerning the continuation, modification, or termination of studies. The PSMB considers study-specific data as well as relevant background knowledge about the disease, test agent, or patient population under study. The PSMB has defined deliberative processes, including event triggers that would call for an unscheduled review, stopping procedures that are consistent with the protocol, unmasking (unblinding), and voting procedures. The event triggers include serious adverse events. The PSMB is also responsible for maintaining the confidentiality of its internal discussions and activities as well as the contents of reports provided to it. On November 9, 2022, Kirabo was presented to the PSMB. At that time, the PSMB had no concerns regarding the performance, monitoring, or safety of the study and recommended the continuation of the study as planned.

All study personnel based in Uganda will be trained in identifying indicators of conditions that may jeopardize the welfare of participants and the limits of confidentiality. This training, conducted by author FS and research staff, focuses on possible scenarios and key questions used to assess risk. Interview staff are trained to err on the side of caution and told to contact the project coordinator and the Masaka diocese in charge of schools, both of whom are always available, via telephone, in the event of the need to break confidentiality owing to an instance of mandatory reporting. Under the guidance of author FS, author OIN, and the parish priest, research staff are trained either to contact the police to ensure the safety of participants or, if appropriate, to have emergency personnel take the adolescent to the nearest hospital.

Adverse events will be reported according to a project protocol. In addition to the PSMB, described earlier, for this study, the PI (PK), the author FS, the project coordinator (author OIN, based in Uganda), and the parish priest (also based in Uganda) will oversee the safety and monitoring of adverse events. This group is expected to meet in person 3 to 4 times per year and will have weekly conference calls. In case of an adverse event, staff will inform the in-country project coordinator and the parish priest immediately and then the US-based PI within 24 hours (with substantial efforts made to also inform the PI immediately) of the occurrence of a possible unanticipated adverse event. Any occurrence of a possible unanticipated adverse event will be immediately reported and brought to the attention of the NYSPI IRB along with the UVRI Research Ethics Board and Ugandan National Council of Science and Technology IRB. The IRBs and PSMB will determine whether it is appropriate to stop the study protocol temporarily or will provide suggestions and modifications for the study procedures. Possible modifications may include adding new risks to the consent form and reconsenting all study participants.

Kirabo aims at HIV prevention and screening for mental health and alcohol use problems. Preliminary outcome data will be examined monthly by the PI (PK) and authors OIN, FS, JSS, and CAM. If preliminary outcome data indicate a harmful impact of the study on the participants (the adolescents), the NYSPI IRB, as well as the Uganda National Council of Science and Technology, will be notified, and it is possible that the study will be discontinued immediately. However, we do not anticipate any negative effects of participation at this time, as much of the proposed intervention is publicly available through m4RH without adverse events. In addition, findings from earlier studies guiding this application suggest an association with positive outcomes, such as increased knowledge of family planning approaches.

### Data Management, Study Oversight, and Monitoring

Human participant protection and data safety are of utmost priority. The primary risk in this study is loss of confidentiality, and there is a possible risk of psychological discomfort or distress arising from the personal and potentially sensitive nature of the information elicited during interviews or intervention sessions. The level and probability of experiencing such risks are minimal, and the monitoring plan described in this paper is commensurate with these risks. All procedures and measures were approved by the UVRI Research Ethics Board and the UNCST as well as the IRBs at the NYSPI and CU and the HIV Center for Clinical and Behavioral Studies PSMB. In addition, the Kirabo intervention was also presented to and approved by the Ugandan Ministry of Health.

## Results

Study recruitment commenced in August 2023 (N=200). Data collection and analysis are expected to be concluded by 2025, respectively. At the time of manuscript submission, no data had been analyzed. This trial was registered with ClinicalTrials.gov (NCT05130151), where the results are expected to be published from 2024 to 2025.

## Discussion

### Principal Findings

Kirabo begins to address the National Institute of Health Office of AIDS Research high priority area of reducing HIV incidence by targeting health disparities and comorbidities, as they challenge the efforts to end the epidemic. The first step in this direction is to promote HIV testing and increase mental health and alcohol use problem screening and linkage to counselors for adolescents and young adults who are symptomatic in regions with a high HIV seroprevalence and limited resources. As described in this protocol, we used the ADAPT-ITT [48] framework to adapt an existing evidence-based mobile phone–delivered sexual health program [54,65,99]. Through this process, including a pretest, we created Kirabo, a pathbreaking approach to link adolescents and young adults to local HIV clinics, PrEP, and mental health and alcohol use problem screening, with referral as needed.

Our pretest results were promising and suggest that it is possible to use school-based recruitment, and the IMB model [49] informed mobile phone SMS text messaging to integrate HIV prevention strategies and mental health care for adolescents and young adults in rural Uganda. The larger population included in our upcoming pilot RCT will provide a clearer understanding of the broad challenges that may impact feasibility and acceptability as well as initial estimates of the intervention effect size.

Mobile phones present an opportunity for contacting, providing information, and motivating adolescents and young adults to seek HIV and mental health care. Although not a panacea, mobile phones have been used for HIV-related sexual health and substance use interventions [100-103] and hold promise for adolescents and young adults who have limited access to the few and frequently overburdened mental health professionals in the region [104,105], specifically in Uganda [18,106,107]. A systematic review of digital innovations for HIV care and prevention noted the need for increased research tailored to context and population to reduce risky behaviors [30]. Furthermore, a review of mobile phone–based interventions in low- and middle-income countries found that they are feasible and improve both HIV and other sexually transmitted infection prevention and care [99]. Notably, a recent systematic review and meta-analysis of digital interventions for common mental disorders in low- and middle-income countries did not include a single study conducted in Africa [108]. The review authors called for future studies “to proactively tackle these challenges and prioritize evaluating digital interventions in low-income countries, especially in Africa, considering its rapidly growing population and potential” [108]. This RCT for evaluating a digital mental health intervention, Kirabo, in Uganda and other recent [109] and ongoing protocols [110] across the continent begin to address this disparity in research.

